## Abstract

*Background*. Lateral elbow pain is one of the most common musculoskeletal pains associated with the upper limb and has an estimated population incidence of 1–3%.* Methods/Design*. This study protocol is for a multisite randomised controlled study and is designed to evaluate the clinical efficacy of acupuncture in the treatment of chronic (over three months' duration) lateral elbow pain. Four study sites, in the People's Republic of China, Hong Kong, Italy, and Australia, will recruit 24 participants each. A total of 96 participants will be randomised to either an acupuncture group or a sham laser control group. The primary outcome measure will be the Disabilities of Arm, Shoulder, and Hand questionnaire with secondary outcome measures of Pain-Free Grip Strength Test, Muscle Tension Test, and a pain visual analogue scale.* Discussion*. Key features for conducting a multisite international acupuncture randomised clinical trial have been detailed in this protocol.* Trial Registration*. This trial is registered at Australian and New Zealand Clinical Trial Registry ACTRN12613001138774 on 11 October, 2013.

## 1. Introduction

Lateral elbow pain (LEP, frequently but incorrectly termed lateral epicondylitis or tennis elbow) is one of the most common musculoskeletal pains associated with the upper limb and has an estimated population incidence of 1–3% [1]. It is a painful condition that is associated with the degeneration in the area of the common extensor tendon of the forearm. Histopathological findings have shown it to be a degenerative condition (tendinosis) of the common extensor tendon, with the extensor carpi radialis brevis tendon more commonly implicated as the primary location of tendinosis. The anatomic basis of the injury to the extensor carpi radialis brevis origin appears to be multifaceted, involving hypovascular zones, eccentric tendon stresses, and a microscopic degenerative response [2].

Optimum treatment of LEP is still debated and research has not been able to determine an optimum treatment [3]. Acupuncture has become increasingly recognised as an alternative treatment for pain, including LEP [4]. In a publication by the United States National Institutes of Health, it was determined that acupuncture may be useful as an adjunct treatment or an acceptable alternative treatment for tennis elbow (lateral elbow tendinosis) [5]. In the past 15 years, acupuncture has become increasingly recognised as an alternative treatment for pain, including pain from lateral elbow tendinosis. However, there is inconclusive evidence that needle acupuncture has a specific action in the treatment of this debilitating condition as shown by Gadau et al. in the latest systematic review on the topic due to low methodological quality and the small sample sizes of the individual studies [6]. The result from a nonrandomised controlled pilot study (*n* = 40) from our group suggests that acupuncture may be helpful in improving function and pain associated with LEP [7]. In this study, the treatment group (*n* = 20) received nine unilateral acupuncture treatments at LI 10 and LI 11 on the affected side with manual needle manipulation while the control group (*n* = 20) received nine sham-laser-acupuncture at the same acupoints. Measures included (i) disabilities of the arm, shoulder, and hand (DASH) questionnaire, (ii) pain-free grip strength (PFGS), and (iii) visual analogue scale (VAS) for pain. Significant differences for the DASH score, PFGS, and VAS between treatment and control group were found after the 8th treatment (*p* < 0.05). Only the DASH scores showed a significant difference between treatment and control group for all time points when measurements were taken which appears to be a sensitive and appropriate primary outcome measure. Results from this pilot study provided relevant information concerning treatment efficacy, credibility of control treatment, and sensitivity of different outcome measures and were subsequently used to develop this protocol.

Furthermore, there have been few international multisite randomised controlled acupuncture trials [8]. This protocol introduces some of the strategies and procedures that have been developed to standardise and remote monitor across sites to ensure the specific key procedures are conducted in accord with the protocol. This randomised clinical trial is designed to evaluate the efficacy of acupuncture in the treatment of chronic (over three months' duration) lateral elbow pain, with specific attentions to overcome some of the limitations of previous studies. The specific hypothesis to be tested in the study is whether acupuncture is more beneficial in improving physical function and reducing symptoms for people with chronic lateral elbow pain of over three months' duration compared to sham laser.

## 2. Methods and Design

### 2.1. Trial Location

The study is to be undertaken at four international sites. These are Changchun University of Chinese Medicine, People's Republic of China; Hong Kong Baptist University, Hong Kong SAR; Paracelso Institute, Italy; and the University of Technology Sydney, Australia. The study will be administered at outpatient clinics attached to each institution. The World Federation of Acupuncture/Moxibustion Societies (WFAS) will coordinate the trial and will be responsible for convening the face to face meetings.

### 2.2. Design

It is a prospective trial that is randomised, controlled, participant/outcome assessor and statistician blinded. It is a multicentre trial with two parallel groups (*n* = 24 at each site, total participants *n* = 96) with a primary endpoint evaluation at completion of the intervention phase (week 3) and a follow-up secondary evaluation three weeks later at week 6. The treatment group will receive traditional Chinese style acupuncture and the control group will receive inactive sham laser therapy to the same local acupuncture points as the treatment group using a modified inactive laser unit.

### 2.3. Randomisation

Randomisation will be performed with a 1 : 1 allocation using a computer generated sequence with the randomisation software Minim [10]. Minim is a program for randomising patients to treatment groups in clinical trials by the method of minimisation, which reduces the differences between the groups for the variables used in the allocation process. Stratification during randomisation will be used based on the participant's gender, age, and the DASH score initially recorded on intake form on recruitment into the study. Allocation concealment will involve a unique three-digit code number known only to the third party randomiser and the practitioner (not outcome evaluator or statistician).

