### 3.4. Control Intervention

The control group will receive inactive sham laser therapy to the same local acupuncture points as the treatment group using a modified inactive laser unit. This was chosen as the control as the inactive device appears to treat acupuncture points with laser light but is inert and does not puncture the skin [9]. The laser probe is rested lightly on the skin and the inactive sham laser will be applied at the same sites for the same duration and order as the acupuncture followed by a rest period of 24 minutes and then a further two minutes of sham radiation to the two acupoints will be administered. Similar to the acupuncture intervention, nine laser sessions will be administered over a three-week period (three treatments per week).

The laser unit will have the laser diode removed. Although the models of the machines will be different between different sites, the following properties will apply: The sham laser must have either light or sound to indicate functionality and be made of stand and probe; when the beam is invisible, it should be referred to as infrared; participants should be warned about the “harmfulness” of laser to the eyes; laser should be held away from their eyes; the trial participants as well as the practitioner should wear special laser-protection glasses.

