### 3.10. Site Monitoring

Each site will digitally video record specific segments of trial processes which will then be uploaded to a secure internet repository for checking against an agreed checklist by clinical trial personnel at the three other sites. The checklist to be used for checking each item of a procedure is shown as follows. A Daily Intervention Reporting Form is to be used to monitor any comments or changes reported by participants. An Adverse Reaction Report Form will be used to record and monitor any adverse events to the interventions and an Incident Report Sheet has been developed to record any injury or incident which affects any person participating in the trail which was not a reaction to the prescribed interventions.

The nine items and their subelements of the video monitor checklist are as follows:Recruitment guidelines
Use of information sheetMeeting recruitment numbers
Interview
Recruitment officer being familiar with the trial protocol and able to answer applicant's questions appropriatelyTrial entry assessment form completed fullyEnrolled applicants meeting eligibility criteriaConsent forms completedConsent forms stored appropriately and separated to participant's folder
Randomisation
Randomisation officer using MINIM software correctlyRandomisation officer stratifying as per allocation and randomisation protocol
Baseline and ongoing data collection
Participant deidentified folders and documentation developed and stored securelyAssessor using correct procedures in regard to scheduling of appointments, interventions, and assessments in accord with the protocolAssessor being familiar with questionnaires and their administrationAssessor being familiar, reliable, and consistent with physical testing equipmentCompetence and consistent in recording test outcomes on appropriate CRFs
Intervention
Ensuring that practitioners be able to adequately measure and mark up acupoints on the participant for treatment in accord with protocolParticipant positioned appropriatelyPractitioners having been trained and each intervention (acupuncture and laser) being delivered correctlyPractitioners knowing the protocol for any adverse reactions and/or how to report an incident
Data collection
Folders being complete with all deidentified filesParticipant folders stored in a secure place
Data entry

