### 3.12. Statistical Evaluation

The statistician will be blind to allocation status and a variety of statistical tests including descriptive and inferential tests (ANOVA, chi square) will be used. A blind third party at the Hong Kong site will undertake the statistical analysis following dual data entry, data checking, and revision. Sample size (*n* = 96, 24 subjects for each site) was based on the China pilot study data associated with the primary outcome, the DASH questionnaire [7] (Liu et al., 2016).

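### Site is not a listed allocation factor, and the article does not say whether Minim runs per site or across sites; state which, and adjust for site

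*Protocol article*

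**What the plan says.** - **Allocation.** Section 2.3 specifies 1:1 allocation by minimisation, "using a computer generated sequence with the randomisation software Minim". The factors are given as "based on the participant's gender, age, and the DASH score" recorded at intake. The same section explains that minimisation reduces differences on the variables it uses. The allocation code is "known only to the third party randomiser and the practitioner"; whether that randomiser is central or local is not stated.
- **Sites.** According to the Abstract, each of four sites "will recruit 24 participants each", 96 in total. No section promises a 12:12 split within a site.
- **Differences between sites.** Section 3.4 on the sham laser says "Although the models of the machines will be different between different sites". Section 2.1 places treatment in a clinic attached to each institution. The Discussion describes English, Chinese and Italian versions of the outcome forms, and makes each site responsible for its own funding, people and equipment.
- **Who operates Minim.** Section 3.10 says "Each site will digitally video record specific segments of trial processes" for the other sites to check, and the checklist includes a randomisation officer's use of Minim.
- **Analysis.** Section 3.12 names ANOVA and chi-square tests without giving a model. Section 3.14 reports that data collection is complete and the analysis has been conducted.

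**The concern.** Minimisation protects balance only on the variables it is given. Here the unlisted variable is one on which the trial plainly differs: the comparator device, the setting, the language of a self-reported primary outcome and, by implication of site-supplied resources, the staff. Balancing on intake DASH may absorb part of a site difference visible at baseline, but not site differences in follow-up scoring or course.

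What is at stake depends on how Minim was operated. In a single run without site, some sites could by chance end with clearly unequal arms, so site-level differences would add error to the unadjusted treatment comparison. In separate runs, sites would be close to balanced. Section 2.3 would then omit a real allocation factor, and an analysis without site would not collect the precision that the balance has earned.

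**Working it through.** **The plan's own figure.** 4 sites × 24 = 96, as stated. Section 3.12 says the size "was based on the China pilot study data associated with the primary outcome", but gives no difference, SD, significance level or power, so that calculation cannot be redone. This point does not depend on it.

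**Inputs for the allocation check.** From the article: 96 participants, four sites of 24, 1:1 minimisation on gender, age and intake DASH. Assumed, because the article does not say: 2 gender, 3 age and 3 DASH levels, equally likely and independent of site; for a single run, random arrival order across sites; the arm that improves balance assigned with probability 1.0 or 0.8. There were 3,000 simulated trials per scenario, and ranges below span the two probabilities.

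| How Minim is run | Mean within-site arm difference (of 24) | At least one site 16:8 or worse | At least one site 15:9 or worse | SD of shift in unadjusted effect, per 1 SD of site effect |
|---|---|---|---|---|
| One run, site not a factor | 3.35 | 30–31% | 59–60% | 0.18 |
| One run, site a factor | 0.6–1.3 | 0–0.2% | 0–3% | 0.045–0.075 |
| Separate run at each site | 0.5–1.1 | 0–0.2% | 0–1.3% | 0.035–0.059 |

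The 0–0.2% entries allow for simulation error; the tabulated runs themselves printed 0 to 0.1%. In the first row, any given site is 16:8 or worse in about 10% of trials.

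**Size of the chance shift in a single run.** With a between-site SD of 0.2 to 0.5 of the within-site SD (assumed), the shift has an SD of 0.178 × 0.2 = 0.036 to 0.178 × 0.5 = 0.089 within-site SDs. For scale, the standard error with 48 per arm is √(2/48) = 0.204 SD. The shift averages zero over randomisations.

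**Cost of ignoring site after separate runs.** Let r be the between-site SD divided by the within-site SD. The true error of the treatment difference then contains almost no between-site part, but an unadjusted standard error still includes it. It is too large by a factor of about √(1 + r²):

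- r = 0.2: √1.04 = 1.020, about 2%
- r = 0.4: √1.16 = 1.077, about 8%
- r = 0.5: √1.25 = 1.118, about 12%

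**Cost of an uneven site.** With 12:12 the variance factor is 1/12 + 1/12 = 0.167. With 8:16 it is 1/8 + 1/16 = 0.188. The ratio of standard errors is √(0.1875/0.1667) = 1.06, so that site's own estimate is about 6% less precise but remains a valid randomised comparison.

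**The case against.** The strongest reply is that Minim was probably operated at each site. The monitoring checklist in 3.10 covers processes that each site records for itself, including the randomisation officer's use of Minim, and the Discussion has each site supply its own resources. Separate runs keep every site nearly balanced without naming site. The checklist also refers to an allocation and randomisation protocol that is not shown and may settle the matter. This stands to a degree: imbalance within sites is conditional and must not be asserted. It does not dispose of the point, because 2.3 gives an explicit list of factors without site, refers to one third-party randomiser, and nothing in the article decides between the two readings.

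Three further objections are right and limit the claim:

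- **Simple randomisation overstates the risk.** Binomial(24, 0.5) gives 15% per site for 16:8 or worse, and 1 − (1 − 0.152)⁴ = 48% for at least one site (77% for 15:9 or worse). The design is minimisation, for which the corresponding figures are about 10%, 30% and 60%.
- **The sham device acts only in the control arm.** Different models would make the treatment effect vary by site, and a 12:12 split would not remove that. It is a reason for showing effects by site, not for balancing on site.
- **Section 3.12 does not exclude site.** It names families of tests, an ANOVA can carry site, and an analysis plan not shown may specify it. It would be wrong to say that the planned analysis ignores site.

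**Conclusion.** The point holds in conditional form. Site is absent from the listed allocation factors, and how Minim was run is undetermined, in a trial whose comparator device, clinics, language versions and resources differ by site.

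- **One run across sites:** about a 30% chance that at least one site is 16:8 or worse (about 60% for 15:9 or worse), and a mean within-site arm difference of about 3.4 of 24. These rest on the assumed factor levels and arrival order.
- **Separate runs:** near balance within sites, but an allocation factor missing from 2.3. If the analysis leaves site out, the standard error is too large by about 2% to 12%, for an assumed between-site SD of 0.2 to 0.5 of the within-site SD.

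A reader might infer that the arms are unbalanced within sites, or that the treatment effect is systematically mixed with site. The documents support neither. The first needs a single pooled run that the article does not state. The second mistakes a chance imbalance, which averages zero and can be adjusted for, for bias. Nor would an uneven site lose its within-site comparison.

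**What to change.** - **Section 2.3:** list site as a minimisation factor, or state that Minim is run separately within each site. As 3.14 reports data collection complete, the allocation can no longer be changed. What is needed now is a statement of how it was actually run, with the arm counts by site.
- **Primary DASH analysis:** include site as a fixed effect. If the completed analysis did not, report the site-adjusted estimate. The cost is three degrees of freedom out of 96 participants.
- **Consistency across countries:** report the treatment effect by site with intervals, as a descriptive check only. With 24 per site these intervals will be wide.

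No new data are required. Had the point been raised before recruitment, the allocation change would have cost one more factor in the Minim set-up.

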### 2.4. Inclusion/Exclusion Criteria

To be included in the study, participants should have chronic lateral elbow pain (duration > 3 months); have unilateral localization of the pain; be between 18 and 80 years of age.

Participants will be excluded if they have a disease of the central or peripheral nervous system; have an inflammatory rheumatic disease; have gout; had an earlier episode of lateral elbow pain treated surgically; have had acupuncture treatment or physiotherapy for tennis elbow within the previous three months or acupuncture treatment for any problems within the previous week or concurrent physiotherapy for tennis elbow.

Figure 1 shows the flow of participants through the study.

## 3. Interventions

The acupuncture administered is based on traditional Chinese medicine (TCM) meridian theory. Two preparative meetings of representatives from our study group had been held to discuss the study protocol, especially the selection of acupuncture and control interventions. Taking into account results of the pilot study, standardisation, and improvement from some previous methodological limitations, a standardised intervention procedure has been developed for both the acupuncture treatment and sham laser control groups. Interventions are not varied for either group; all participants will receive the same treatment at all sessions for their group. Only the affected arm is treated. Practitioners are required to apply a standardised intervention procedure to participants dependent on the participant's randomisation status. Acupoint selection was based on a consensus by all four recruiting centres following positive outcomes from the analysis of data generated from a pilot study undertaken by one of the research groups at Changchun University of Chinese Medicine [7].

All acupoints are to be marked with a semipermanent ink. The two acupoints are to be located as described in the* WHO Standard Acupuncture Point Locations in the Western Pacific Region* [11]. The acupoint Large Intestine (LI) 11 (Quchi) is located on the lateral aspect of the elbow, at the midpoint of the line connecting Lung 5 (Chizi) with the lateral epicondyle of the humerus. The acupoint LI 10 (Shousanli) is located on a line connecting LI 5 (Yangxi) (on the posterolateral aspect of the wrist, at the radial side of the dorsal wrist crease, distal to the radial styloid process, in the depression of the anatomical snuffbox) with LI 11 (Quchi), 2 body units (cun) inferior to the cubital crease on the forearm. The acupoint LI 10 will be located using a piece of elastic divided into 12 equal proportions to assist accurate proportional measurement [12].

### 3.1. Acupuncture

Single-use, stainless steel, presterile filiform 0.30 mm × 40 mm Hua Tuo brand needles will be used to needle the acupoint sites following cleansing of the skin with rubbing alcohol.

### 3.2. Needle Manipulation

The acupoint LI 11 will be needled first, perpendicular deep insertion up to 1.5 body units (cun), and then withdrawn to 1 cun depth. Following insertion, the traditional needle technique of “Wagging the Dragon's Tail” (WDT) will be performed. This involves holding the needle on distal end of the handle and bending it 45° left and then right with a speed of 1 Hz for 2 minutes or to the participant's tolerance. Then, the acupoint LI 10 will then be needled using oblique insertion at 45 degrees angled towards the elbow and the same needle technique of WDT applied for the same period of time (2 minutes) or to the patient's tolerance. Whenever the duration of needle manipulation is less than the required time of 2 minutes (due to patient request to stop due to excessive pain or sensation), a note will be kept of the time the technique was applied. Needling sensation (deqi) will be sought on both acupoints. Muscle twitch will be recorded on participant's daily reporting sheet if achieved on acupoints LI 10 and/or LI 11.

The needles will be retained for a further period of 24 minutes and then the process of needle manipulation will be repeated at each site and needles will be withdrawn. In total, the needles will remain in situ for 28 minutes. Nine acupuncture treatments will be administered over a three-week period (three treatments per week).

### 3.3. Online Training Video for Acupuncturists

A video of the needle technique (needle insertion and the technique of “Wagging the Dragon's Tail”) has been uploaded onto the cloud repository for review by all the needling research teams. This is to assist in standardising the intervention needling technique. All practitioners of needling had at least seven years of clinical experience and were credentialed as registered or licensed practitioners.

